### Determination of sample size

Although a standard power calculation based on detecting treatment effects is the conventional approach to determining sample sizes for definitive clinical trials, the main aim of the current pilot trial is to investigate the core protocol and procedural uncertainties, in preparation for a later scaled up evaluation of the intervention in line with current guidance [20]. Nonetheless, we will obtain working knowledge of the likely effect size of the intervention itself. Seventeen participants per arm (TF-CBT-YC versus TAU) is enough to detect a difference in the recovery percentage as small as 44% on the DIPA diagnosis of PTSD, with 80% power at the 1-tailed 5% level of significance (45% in TAU versus 89% in TF-CBT-YC). These figures fall within the intent-to-treat outcomes in our previous trial in older children [18] (WL: 42% versus TF-CBT: 92%). These group sizes would also detect differences as small as 1.0 standard deviation (SD) unit on our continuous outcome of PTSD symptomatology, given the same power and level of significance. This would have provided sufficient power to detect group differences both in our previous trial [18] (adjusted effect size: Child PTSD Symptom Scale [21] = 2.48 SD units) and in the New Orleans trial [17] (adjusted effect size: PTSD symptom count = 1.32 SD units). To account for 20% potential attrition we will, therefore, recruit 22 young children per arm to the trial. It is important to note that the use of a half-crossover design with the initial TAU participants being offered TF-CBT-YC augments the sample size for the pre- to post-treatment comparisons on outcomes.

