### Statistical analysis plan

Initial analyses of the quantitative primary and secondary outcome data will be conducted on an intent-to-treat basis, with subsequent analyses being per protocol (based on attendance at 50% of offered sessions), and carried out by the trial statistician (PW) following CONSORT standards [33]. Comparisons will be made across groups on all outcome measures. For the continuous scales, repeated measures analyses of variance (ANOVAs) will be used without adjustment in the first instance, and then adjusting for baseline levels of the relevant measures as covariates if indicated. For the caseness measure of PTSD, non-parametric analyses will be used (for example, Chi square/Fisher’s exact test).

Qualitative interview data will be analysed using thematic analysis [34], facilitated by NVivo 8 software (QSR International). For the health economic data, mean estimated treatment costs in the two trial arms will be compared using ANOVA and the robustness of the parametric tests confirmed using bootstrapping. The primary analysis will explore cost-effectiveness in terms of loss of PTSD diagnosis (that is 'recovery'). If a significant difference in the primary outcome is observed between the two treatment arms, cost-effectiveness will be explored through calculation of an incremental cost-effectiveness ratio and sensitivity analyses.

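### For the continuous secondary scales, unadjusted repeated-measures ANOVA is a poor first-line intent-to-treat analysis when 20% attrition is expected; a prespecified baseline-adjusted mixed model should replace it

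*Protocol article*

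**What the plan says.** All references are to the protocol article.

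- **Statistical analysis plan, population:** "Initial analyses of the quantitative primary and secondary outcome data will be conducted on an intent-to-treat basis". Per-protocol analyses follow, defined by attendance at half of the sessions offered.
- **Statistical analysis plan, continuous scales:** "repeated measures analyses of variance (ANOVAs) will be used without adjustment in the first instance". Adjustment for baseline comes second, and only where it is judged to be needed.
- **Statistical analysis plan, primary outcome:** "For the caseness measure of PTSD, non-parametric analyses will be used (for example, Chi square/Fisher’s exact test"). These tests are given as examples.
- **Determination of sample size:** "Seventeen participants per arm (TF-CBT-YC versus TAU) is enough to detect a difference in the recovery percentage as small as 44"%, "with 80% power at the 1-tailed 5% level of significance (45% in TAU versus 89% in TF-CBT-YC"). Then: "To account for 20% potential attrition we will, therefore, recruit 22 young children per arm to the trial".
- **Secondary clinical outcomes:** both arms complete the scales at baseline and post-treatment. Only the treated arm completes them at 3 and 12 months.
- **Participant allocation:** minimisation on age group, gender and baseline DIPA severity.

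**The concern.** The article names a specific method for the scales and puts it under an intent-to-treat heading. In its classical form that method works on complete rows: a child without one of the modelled visits leaves the analysis. The sample-size section expects losses of about one child in five, so the exclusion is foreseeable.

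Leaving baseline unadjusted at first has two further effects. It gives up precision in a trial with about 17 children per arm analysed. It also leaves the between-arm contrast open to bias if children who drop out of one arm differ at baseline from those who stay. One arm is asked to attend 12 sessions and the other waits for an offer of therapy, so losses of different kinds in the two arms are plausible, although the article gives no data on this.

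Making adjustment conditional also leaves the choice between two analyses open until the data are seen.

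**Working it through.** **1. The plan's own figures.** Inputs from Determination of sample size: 17 per arm, 45% v 89%, one-tailed 5%, 20% attrition.
- Exact enumeration of one-tailed Fisher's test at 17 per arm gives power of 81.4% (stated: 80%).
- For 1.0 SD at 17 per arm, t-test power is 89% one-tailed and 81% two-tailed.
- 17 / 0.8 = 21.25, rounded up to 22.

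All of these reproduce. The planned loss is 22 − 17 = 5 per arm, or up to 10 of 44.

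**2. What the ANOVA tests.** The arms share two visits. With two visits, the arm-by-time F test is the square of the t test on change scores. A child needs both scores to enter.

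**3. Precision.** Let ρ be the correlation of baseline and post-treatment scores and σ their common SD. The article gives no ρ, so 0.4 to 0.8 is assumed.
- Variance of a change score: 2(1 − ρ)σ².
- Variance after baseline adjustment: (1 − ρ²)σ².
- Ratio: (1 + ρ)/2, so the SE ratio is √[(1 + ρ)/2].

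| ρ | SE ratio | SE reduction | Change-score n per arm equivalent to 17 adjusted |
|---|---|---|---|
| 0.4 | √0.70 = 0.837 | 16% | 17/0.70 = 24.3 |
| 0.6 | √0.80 = 0.894 | 11% | 17/0.80 = 21.3 |
| 0.8 | √0.90 = 0.949 | 5% | 17/0.90 = 18.9 |

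These are large-sample values. Estimating the slope gives back a small part at this size.

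**4. Bias from baseline-related loss.** With no treatment effect, a child at b SD from the baseline mean has an expected change of −(1 − ρ)b. If treated-arm completers have a mean baseline s SD lower than all treated children, and loss in TAU is random, the change-score contrast is off by (1 − ρ)s. The adjusted contrast is not, provided the regression on baseline is linear.

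The sharpest case for 20% loss is that exactly the most severe fifth leave: s = φ(0.842)/0.8 = 0.280/0.8 = 0.35. The bias is then 0.6 × 0.35 = 0.21, 0.4 × 0.35 = 0.14 or 0.2 × 0.35 = 0.07 SD at ρ = 0.4, 0.6 or 0.8. Weaker dependence gives proportionally less.

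A simulation with 22 per arm and treated-arm loss depending on baseline gave 0.07 to 0.16 SD. The adjusted model removed this and had a standard error about 5% to 16% smaller. The direction is not fixed: losing the most severe treated children works against TF-CBT-YC, and losing the mildest works for it.

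**5. Primary diagnosis, to scale a sensitivity analysis.** Suppose 45% recover in both arms, TAU loss is random, and the 20% lost from TF-CBT-YC would have recovered at rate q. TF-CBT-YC completers show (0.45 − 0.2q)/0.8. If only completers were analysed, 17 per arm, the one-tailed Fisher rejection rate would be:

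| q | Completers' rate | Rejection rate |
|---|---|---|
| 0% | 56.25% | 10.7% |
| 10% | 53.75% | 8.2% |
| 20% | 51.25% | 6.2% |
| 30% | 48.75% | 4.6% |
| 45% | 45% | 2.8% |

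For the uncorrected chi-square test the rate is 15.0% at q = 10% and 6.0% at q = 45%.

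One-tailed power with all 22 per arm analysed, starting from 45% v 89%:

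| Assumption about missing outcomes | Rates compared | Fisher | Chi-square |
|---|---|---|---|
| 20% missing in each arm, counted as still PTSD | 36% v 71.2% | 66% | 77% |
| 10% missing in each arm, counted as still PTSD | 40.5% v 80.1% | 78% | 87% |
| 20% of TF-CBT-YC lost, recovering at the TAU rate | 45% v 80.2% | 68% | 80% |
| 20% missing in TF-CBT-YC only, counted as still PTSD | 45% v 71.2% | 42% | 55% |

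Every dropout outcome in this step is an assumption.

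**The case against.** The point concerns secondary outcomes in a pilot whose stated main aim is not hypothesis testing. The article contrasts intent-to-treat with a per-protocol set defined by attendance, so the term may mean only that children are analysed as randomised whatever they attended. A family that leaves therapy can still complete parent-report measures. A missing-data rule may sit in a full plan that is not shown. And with two shared visits, a mixed model with baseline as a covariate gains nothing from a child who has no post-treatment score.

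Most of this stands and limits the point. The mixed model recovers few or no children for the between-arm contrast. Its gain comes from baseline adjustment and from validity when loss depends on observed data. It does not cure loss that depends on the unseen outcome. What remains is that the article itself fixes the method, and that the unadjusted form is the weaker choice under the attrition it expects.

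A reader might go further and infer that the whole analysis, primary outcome included, is complete-case and that the 80% power is therefore misstated. The documents do not support this:
- No section says that children without a diagnosis are dropped.
- Chi-square and Fisher's test are only examples, and can be run on all 44 once missing diagnoses are assigned.
- The sample-size section already ties the 80% to seventeen per arm, and inflating for attrition is standard practice.
- On the assumed recovery rates it says: "These figures fall within the intent-to-treat outcomes in our previous trial in older children". So they are not presented as completer rates.

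**Conclusion.** The concern holds for the continuous secondary scales. Unadjusted repeated-measures ANOVA, as the first-line intent-to-treat analysis with up to 10 of 44 children expected to be lost, keeps only complete rows. It is less precise, and more open to bias from baseline-related dropout, than an adjusted model.

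The size is modest. The standard error is reduced by about 5% to 16% for an assumed correlation of 0.8 down to 0.4. The avoidable bias was 0.07 to 0.16 SD in simulation, with 0.21 SD as the closed-form extreme at a correlation of 0.4, against a design difference of 1.0 SD. The bias figures require loss in the treated arm to depend on baseline, which the article neither states nor rules out.

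For the primary diagnosis there is no demonstrated error. The figures in step 5 show how far results could move under assumed dropout outcomes. They support a sensitivity analysis and do not show that the plan's power or test is wrong.

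**What to change.** **Continuous scales.** Replace the repeated-measures ANOVA with one prespecified likelihood-based linear mixed model:
- terms for arm, time and arm × time, with age group, gender and baseline DIPA severity as covariates;
- baseline score as a covariate, or as a response with a common baseline mean in both arms. If the baseline means are left free by arm, the contrast with complete data is the change-score comparison again and the precision gain is lost;
- small-sample degrees of freedom;
- all available data from every randomised child, with the missing-at-random assumption stated.

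Make the adjusted analysis the only first-line one, so that adjustment no longer depends on a later judgement. Say that the 3- and 12-month scores, collected only in the treated arm, do not determine who enters the between-arm comparison at post-treatment.

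**Primary diagnosis.** Add a supporting sensitivity analysis of all 44 as randomised, with missing counted as still PTSD and with a range of assumed recovery rates for dropouts that may differ by arm.

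**Sample size.** No change is needed.

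**Cost.** A slightly more complex model, a little extra analysis and revised wording. No new visits, data or recruitment.

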### Participant allocation

Eligible participants will be randomised to TF-CBT-YC or TAU using a minimisation procedure suitable for small samples, constrained by age group (3 to 5 years or 6 to 8 years), gender, and initial clinical severity as assessed on the DIPA (high and low). These variables were selected because of their likely influence on treatment response. Randomisation will occur after consent has been taken and baseline measures have been completed. The trial team will Email the independent statistician (PW) details of the three stratifiers and, using the minimisation programme MinimPy [22], the statistician will randomise the participant and Email the results to the trial coordinator. Following randomisation, participants will be notified of their allocation by telephone, which is subsequently confirmed in writing. See Figure 2 for the Consolidated Standards of Reporting Trials (CONSORT) diagram.

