### Measures

#### Primary clinical outcomes

The primary outcome will be recovery from PTSD using the DIPA at post-treatment. The DIPA is a psychometrically robust parental report semi-structured interview designed for this age group [19].

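### Allocation is minimised on three factors expected to affect response, but the tests named for the primary outcome ignore them; if the factors matter, the crude test is mildly conservative

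*Protocol article*

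**What the plan says.** Under Participant allocation, randomisation uses minimisation "constrained by age group (3 to 5 years or 6 to 8 years), gender, and initial clinical severity", the last split into high and low on the DIPA. The reason follows: "These variables were selected because of their likely influence on treatment response".

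Under Primary clinical outcomes: "The primary outcome will be recovery from PTSD using the DIPA at post-treatment". This is a yes/no outcome.

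Under Statistical analysis plan, the method for that outcome is: "For the caseness measure of PTSD, non-parametric analyses will be used", with chi-square and Fisher's exact test given as examples. The section mentions adjustment only for the continuous scales, which are first analysed unadjusted, "then adjusting for baseline levels of the relevant measures as covariates if indicated". It does not say that the minimisation factors enter the analysis of PTSD caseness.

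Determination of sample size gives 17 per arm for 45% versus 89% recovery, with 80% power at a one-tailed 5% level, raised to 22 per arm for 20% attrition.

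**The concern.** Minimisation makes the arms alike on the chosen factors. If those factors predict recovery, the difference in recovery proportions varies less from trial to trial than under simple randomisation. A crude 2x2 test does not know this. Its reference variance still contains the part of the outcome variation that the allocation has balanced away, so its p-values tend to be too large.

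The protocol supplies the premise itself: the factors were chosen because they were expected to matter. If they do, an analysis that leaves them out gives up some of the precision that the allocation was meant to provide.

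The result has uses beyond a single p-value. The incremental cost-effectiveness ratio is calculated only if the primary comparison is significant. The trial is also meant to give a working idea of the effect size, and the Discussion ties the case for a definitive trial to showing superiority over TAU. With 44 children, about 34 after attrition, precision that costs nothing is worth having.

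**Working it through.** **Inputs from the protocol.** 17 per arm, one-tailed 5%, 45% versus 89%, 20% attrition, 22 per arm (Determination of sample size); three two-level minimisation factors (Participant allocation).

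**Assumptions, because the protocol gives no figures.** The same odds ratio for each factor (1, 2, 4 or 8); each factor split 50:50; a biased-coin probability of 0.9 in the minimisation.

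**Step 1: reproduce the plan's figure.** The exact power of a one-sided Fisher test is the sum, over all outcome pairs (a, b) with p ≤ 0.05, of Bin(a; 17, 0.45) × Bin(b; 17, 0.89). This gives 0.8135, in line with the stated 80%. Attrition: 17 / (1 − 0.20) = 21.25, rounded up to 22, as stated. The sample size is therefore consistent with an unadjusted one-sided Fisher test. A one-sided uncorrected chi-square test with the same 17 per arm has exact power 0.897. Fisher thus trails chi-square by 0.897 − 0.8135 = 0.0835, about 8 points, before any prognostic factor is considered.

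**Step 2: the mechanism.** The crude statistic is z = (p1 − p0) / √[p(1 − p)(1/n1 + 1/n0)], where p is the pooled proportion. Balancing a prognostic factor shrinks the true spread of the numerator and leaves the denominator unchanged, so under the null z varies less than a standard normal. The adjusted comparison fits Y = α + τ·arm + β1·age + β2·gender + β3·severity by least squares and tests τ (the risk difference) against its residual standard error on a t distribution.

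**Step 3: size of the effect.** Simulated minimised trials, 5,000 per cell, one-sided 5%. Size is at a common recovery rate of 45%; power is at 45% versus 89%. All entries are percentages, and gains are in points.

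| Total N | OR per factor | Size: chi-sq / Fisher / adjusted | Power: chi-sq / Fisher / adjusted | Gain over chi-sq | Gain over Fisher |
|---|---|---|---|---|---|
| 34 | 1 | 5.7 / 2.8 / 4.9 | 90.2 / 82.7 / 90.0 | −0.2 | 7.3 |
| 34 | 2 | 5.6 / 2.4 / 5.2 | 90.6 / 83.1 / 91.3 | +0.7 | 8.2 |
| 34 | 4 | 4.0 / 1.5 / 4.8 | 92.0 / 84.0 / 94.1 | +2.1 | 10.1 |
| 34 | 8 | 2.4 / 0.9 / 4.7 | 92.9 / 84.8 / 95.9 | +3.0 | 11.1 |
| 44 | 1 | 5.0 / 2.6 / 5.0 | 95.6 / 90.6 / 95.0 | −0.6 | 4.4 |
| 44 | 2 | 4.3 / 1.9 / 5.1 | 95.5 / 90.7 / 95.7 | +0.2 | 5.0 |
| 44 | 4 | 3.6 / 1.4 / 5.5 | 96.8 / 92.3 / 97.6 | +0.8 | 5.3 |
| 44 | 8 | 2.1 / 0.7 / 5.3 | 97.6 / 93.6 / 99.0 | +1.4 | 5.4 |

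The Monte Carlo standard error is √(0.05 × 0.95 / 5000) = 0.3 points for size and √(0.9 × 0.1 / 5000) = 0.4 points for power near 90%.

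The size of both crude tests falls as the factors become more prognostic, while the adjusted model stays near 5%. Of Fisher's 10.1-point deficit at N = 34 and OR 4, 7.3 points are already there at OR 1. That part is discreteness.

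**Step 4: which adjusted analysis.** The expected number not recovered at 17 per arm is 17 × 0.55 + 17 × 0.11 = 9.35 + 1.87, about 11 children, with about 2 in the TF-CBT-YC arm. This rules out heavy modelling.
- A likelihood-based logistic score test on the same simulated data, without Firth's correction, was slightly liberal (size 5.3% to 7.0%).
- A Mantel-Haenszel test on the four severity-by-age strata was simulated with 44 children minimised and a random loss to 34 (6,000 trials per cell, one-sided 5%). Power for chi-square versus Mantel-Haenszel was 90.0 v 87.9 with no factor effects, 89.7 v 88.6 with both odds ratios 2, 90.2 v 90.2 with severity 3.5 and age 2, and 91.4 v 91.8 with severity 5.6. Cross-stratifying so few children gains almost nothing and loses 1 to 2 points when the factors are weak.

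**The case against.** The strongest reply has four parts.

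- **The tests are only examples.** The wording does not exclude an adjusted analysis, and covariate detail is often left to a fuller document. This stands in part: it would be wrong to say that the plan rules adjustment out. But the article has a section on the statistical analysis that names the kind of test for the primary outcome and reserves adjustment for the continuous scales. The point is about what is stated there.
- **The error is on the safe side, in a pilot.** This stands. The protocol puts procedural uncertainties first and leaves the definitive answer to a later trial. Ignoring the factors lowers the false-positive rate. Chi-square's small excess with 17 per arm and no factor effects (exact size 5.98% at 45%) is a small-sample approximation error, not a result of minimisation.
- **The gain is small and depends on unknown factor strength.** This stands, and it sets the size of the point. Loss of children after allocation would also erode the balance; the table assumes complete follow-up of the N shown.
- **Adjustment has its own risks with about 11 non-recoveries.** This stands, and it determines the form of the fix.

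A reader might go further and infer that the trial is underpowered, because a two-sided 5% Fisher test with 17 per arm has power of only 70% (exact 0.7027). The protocol states a one-tailed 5% level, at which Fisher has 81%, so the two-sided figure is not the power of the planned test. A reader might also say that the reported confidence interval will be too wide. The protocol specifies no interval for the primary outcome, so none can be faulted.

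**Conclusion.** The point holds in a modest form. The protocol allocates on three factors because it expects them to matter, and then names tests for the primary outcome that leave them out. If they are prognostic, the crude test is mildly conservative.

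At one-sided 5% and assumed odds ratios of 1 to 4 per factor, linear adjustment is worth about −1 to +2 points of power against chi-square. It is worth about 4 to 10 points against Fisher (11 at an odds ratio of 8, N = 34), mostly because Fisher is discrete. The stated 80% power at 17 per arm is met either way, and the sample size is not in question.

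These figures rest on assumed factor effects, 50:50 splits and a 0.9 biased coin, none of which the protocol gives. The direction follows from the design; the size does not. This is an inexpensive improvement, not a flaw that threatens the trial's conclusions.

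**What to change.** Pre-specify the primary comparison along these lines: the difference in PTSD recovery at post-treatment (TF-CBT-YC minus TAU) will be estimated with adjustment for age group, gender and baseline DIPA severity group as used in the minimisation, by a linear risk-difference model, and reported with a 95% confidence interval; the unadjusted 2x2 Fisher or chi-square test will be a sensitivity analysis.

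Firth logistic regression on the same three factors, with a standardised risk difference and 95% confidence interval, is a reasonable alternative. Only the linear model was simulated here, so the Firth version should be checked in the same way before it is adopted.

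Do not use a fully cross-stratified Mantel-Haenszel test, and do not add acute or chronic status as a further covariate. With about 11 expected non-recoveries the data will not support either.

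The change takes a sentence or two and needs no new data, since all three factors are recorded before allocation. It costs a slightly less simple presentation than a 2x2 table and possibly about 1 point of power against chi-square if the factors turn out not to be prognostic.

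### The primary recovery comparison is given two example tests; at 17 to 22 per arm one is conservative and the other slightly liberal, and one named unconditional exact test would do better

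*Protocol article*

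**What the plan says.** Under Primary clinical outcomes, the protocol article states: "The primary outcome will be recovery from PTSD using the DIPA at post-treatment". This is a yes/no outcome compared between two arms. For its analysis, the Statistical analysis plan section says: "For the caseness measure of PTSD, non-parametric analyses will be used (for example, Chi square/Fisher’s exact test"). That sentence gives no rule for choosing between the two, no tail, and no word on a continuity correction.

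Determination of sample size gives the planning figures: "Seventeen participants per arm (TF-CBT-YC versus TAU) is enough to detect a difference in the recovery percentage as small as 44" percentage points, "with 80% power at the 1-tailed 5% level of significance", with assumed rates of "45% in TAU versus 89% in TF-CBT-YC". It names no test. Recruitment is raised to 22 per arm for 20% attrition. The same section says that "we will obtain working knowledge of the likely effect size of the intervention itself".

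One later step depends on the verdict of this test. The incremental cost-effectiveness ratio is calculated on this condition: "If a significant difference in the primary outcome is observed between the two treatment arms". The Discussion also ties the case for a definitive trial to superiority being shown.

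**The concern.** Chi-square and Fisher's exact test are close to interchangeable in large samples, but not with about 20 children per arm. Fisher's test conditions on the total number recovered. Few tables are then possible, so its true error rate lies well below the nominal level and power is lost. Uncorrected Pearson chi-square uses a normal approximation, which can exceed the nominal level at this size. If both remain open until the data are in, a borderline result can be significant or not depending on which is run, and with it whether the cost-effectiveness ratio is calculated.

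A third test holds the level and recovers most of the power that Fisher gives up. The plan could name it at almost no cost.

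**Working it through.** **Inputs.** From Determination of sample size: 17 evaluable and 22 recruited per arm, one-tailed 5%, recovery of 45% versus 89%, and the earlier trial's rates ("WL: 42% versus TF-CBT: 92"%). The rates 45% versus 80% and 45% versus 75% are my assumptions, to show a smaller effect.

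**Method.** With n per arm, let *a* be the number recovered on TAU and *b* on TF-CBT-YC. Every table (18 × 18 or 23 × 23) is enumerated with probability Bin(*a*; n, p₁) × Bin(*b*; n, p₂). Each test is applied to each table:

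- Fisher: p = Σ over x ≥ *b* of C(n, x)·C(n, *a*+*b*−x) / C(2n, *a*+*b*).
- Uncorrected chi-square, one-sided: z = (*b*−*a*)/n ÷ √[p̄(1−p̄)·2/n], with p̄ = (*a*+*b*)/2n; reject if z ≥ 1.645.
- Boschloo: the probability of a Fisher p-value at least as small as the one observed, maximised over the common recovery rate.

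Size is the rejection probability with p₁ = p₂, maximised over the common rate. Power is the same sum at the stated rates.

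**The plan's own figure.** One-sided Fisher at 45% versus 89% has power 77.6% with 16 per arm and 81.4% with 17, so 17 is the smallest number reaching 80%. Attrition: 17 / 0.8 = 21.25, rounded up to 22. The stated figures reproduce. (A two-sided uncorrected formula also gives 17, with 80.8% power, so this does not prove which test was meant.)

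**Size and power, one-tailed 5%.**

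| | Fisher | Chi-square, uncorrected | Boschloo |
|---|---|---|---|
| Maximum size, 17 per arm | 2.9% | 6.1% | 4.5% |
| Maximum size, 22 per arm | 2.5% | 5.55% | 4.9% |
| Power 45/89, 17 per arm | 81.4% | 89.7% | 88.5% |
| Power 45/89, 22 per arm | 90.6% | 95.7% | 94.8% |
| Power 45/80, 17 per arm | 58% | 72% | 68% |
| Power 45/75, 17 per arm | 45% | 59% | 53% |
| Power 45/75, 22 per arm | 53% | 66% | 65% |

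Boschloo rejects every table that Fisher rejects. Its gain at 45/89 is 88.5 − 81.4 = 7.1 points (17 per arm) and 94.8 − 90.6 = 4.2 points (22 per arm). The largest gain in the table is 65 − 53 = 12 points.

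**How often Fisher and uncorrected chi-square disagree.**

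| True recovery | 17 per arm | 22 per arm |
|---|---|---|
| 45% vs 89% | 8.3% | 5.1% |
| 45% vs 80% | 13.5% | 11.7% |
| 45% vs 75% | 14.4% | 13.2% |
| 42% vs 92% | 4.5% | 1.9% |
| 45% vs 45% | 3.2% | 2.4% |

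In every split it is chi-square that rejects. The continuity-corrected chi-square gives the same one-sided verdict as Fisher at both sizes.

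**One table.** Take 15/17 versus 10/17. Then p̄ = 25/34 = 0.735, the difference is 5/17 = 0.294, and the standard error is √(0.735 × 0.265 × 2/17) = 0.151. So z = 1.94 and p = 0.026. Fisher gives 0.059 and Boschloo 0.030.

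**The case against.** The strongest reply is scope. A journal article condenses a fuller plan, the phrase is openly an example, both tests are conventional, and the choice between them is commonly settled in the analysis plan. That stands as far as the open choice goes: alone it would not be a finding. What remains is that neither example is the best method at this size, and a better one takes a sentence.

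A reader might infer more than the documents support:

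- *That the trial is underpowered because Fisher is conservative.* It is not, by its own target. The stated 80% is met by one-sided Fisher at 17 per arm, so its conservatism is already paid for.
- *That about one trial in ten of this size would give conflicting verdicts.* The range 8-14% needs 17 evaluable per arm, uncorrected chi-square, and a true effect between 45/89 and 45/75. With all 22 per arm evaluable, the figure at the planning rates is 5.1%.
- *That chi-square seriously breaks the 5% level.* The excess is about one point at 17 per arm and about half a point at 22. At 22 per arm and a common rate of 45%, the size is 4.85%. The continuity-corrected version does not overshoot, and the article does not say which version is meant.
- *That the data would choose the test, through the customary switch to Fisher when an expected count is below 5.* No such rule is in the article.
- *That no effect size would be available.* Two recovery percentages give the difference directly, and the article commits to CONSORT reporting. Stating an interval only makes that explicit.

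It is also fair to say that the stakes are limited. This is a pilot whose main declared aim is procedural, and the economic estimates are described as preliminary.

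**Conclusion.** The point holds as a modest improvement to the method, not as an error in the plan. Of the two example tests, Fisher uses only about half of the 5% (at most 2.9% or 2.5%), and uncorrected chi-square slightly exceeds it (at most 6.1% or 5.55%). Boschloo's test keeps within the level at both sizes and gains roughly 4 to 12 points of power over Fisher for true effects between 45/89 and 45/75. Nearer the earlier trial's 42% versus 92%, all three tests have high power and the choice matters less.

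These figures assume independent binomial outcomes, equal arms, a one-tailed 5% level as in the sample size section, and no allowance for the minimisation factors. The analysis sentence itself states no tail. If the test were two-sided, Fisher and uncorrected chi-square would disagree at 45/89 in 11.2% (17 per arm) or 6.1% (22 per arm) of trials. Whether one tail is appropriate is a separate question.

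**What to change.** Before outcome data are seen, replace the parenthetical example in the Statistical analysis plan section with one named test: Boschloo's unconditional exact test, at the tail and level given under Determination of sample size. State beside it that the difference in recovery percentage will be reported with a 95% confidence interval (for example Newcombe or Miettinen-Nurminen). Say that the interval is for estimation, since a two-sided 95% interval need not agree with a one-tailed 5% test.

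The cost is one or two sentences, with no new data and no change to the sample size. The downside is a test less familiar to readers than Fisher's, though standard software has it. If the team prefers a familiar test, naming one-sided Fisher alone would remove the ambiguity and still meet the stated 80%, at the price of the power shown above.
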